While the reported treatment effects of Internet-based CBT for treating adolescent anxiety are promising [33,34], published systematic reviews highlight important methodological issues that future studies must consider, in order to mature the evidence base [30,31,32]. Two reviews reported that the overall quality of the outcomes reported by studies of computerized CBT, including Internet-based CBT for adolescents, was *low* to *very low* [30,32]. Key limitations of the evidence base that were identified included: small sample sizes, intervention and comparator (waitlist or active control) differences between studies, and inconclusive treatment effects when anxiety was self-rated (versus clinician rated) [30,31,32]. Many of these limitations were also noted in the Tillfors and Spence studies [33,34]. Reviews to date have recommended that higher quality evidence is needed to firmly establish the treatment effects of computerized CBT, and that the study of associated economic impacts is needed [30,31,32].

We designed a pilot randomized controlled trial (RCT) that addresses several of the limitations highlighted in the literature to date. This pilot trial aims to collect the necessary data to inform the planning of a full-scale RCT to test the effectiveness of the Internet-based CBT program *Breathe* (Being Real, Easing Anxiety: Tools Helping Electronically). In the pilot RCT we will (1) define a minimal clinically important difference (MCID), as defined by adolescents, for the primary outcome measure, (2) determine a sample size for a full-scale RCT, (3) estimate recruitment and retention rates to determine the number of study sites needed, (4) measure intervention acceptability to inform critical intervention changes, (5) determine the use of co-interventions, and (6) conduct a cost-consequence analysis to inform a cost-effectiveness analysis for a full-scale RCT.

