#### Secondary Outcome Measures

All secondary outcome data are collected via self-report using IRIS. The MCID will be determined for the primary outcome measure following module 8 completion (post-intervention). Adolescents allocated to the treatment condition are asked to indicate the minimum change in anxiety for which they would consider treatment participation. We will use the MCID to guide interpretation and application of outcome change in a full-scale RCT. To estimate the MCID, we will use adolescents’ global ratings of change on a 10-point Likert scale (-5 to +5), a commonly used anchor [44,45].

Satisfaction will be measured in adolescents allocated to the treatment condition at the end of module 8 (post-intervention) to infer intervention acceptability. A 12-item instrument developed by the research team will measure satisfaction based on the adolescent’s report of the program’s engagement and sense of safety/privacy, expectations and usefulness, communication, and technical (intervention) management. For 10 statements, a 5-point Likert response format ranging from strongly agree (score 5) to strongly disagree (score 1) will be used. Scores range from 10 to 50 with scores of 40 or greater indicating higher acceptability. Two open-ended questions to inform the larger trial will allow adolescents to identify challenges or barriers that were faced in taking part in the trial, and the extent to which adolescents used the skills learned.

Treatment adherence will be measured at 8 weeks to further evaluate intervention acceptability. Adherence is measured by documenting the number of treatment modules and homework tasks completed. We will also record the number of tailored modules completed by each participant (treatment arm) and site visits (control arm). These data are being collected through IRIS.

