### Statistical Analyses

Adolescent reports of anxiety, intervention acceptability and adherence, use of co-interventions, recruitment and retention rates, and demography will be described by numerical summaries (mean, frequency, range, and standard deviation [SD]). The mean difference in primary outcome change scores (and SDs) from baseline to the completion of module 8 (post-intervention) will be calculated with 95% CIs. SD values from the primary outcome change scores will be used to guide the full-scale RCT sample size calculations [51]. Adolescent global ratings of change (within the ranges of +2 to +3 or -2 to -3 for reported change using the 10-point Likert scale) will serve as the estimate for the MCID value [52]. The study recruitment rate (number of adolescents enrolled during the study recruitment period) and the retention rate (number of adolescents retained at the 3-month follow-up as indicated by MASC2 completion) will be calculated. These rates will be used to determine the number of study sites and time period needed for a full-scale RCT. Frequencies and proportions (with 95% CIs) will be used to describe categorical variables (eg, gender). We will summarize characteristics of completers (>75% of modules) and non-completers, and conduct tests of association to identify particular adolescents (eg, by gender) that may benefit from additional measures to maintain engagement, and will explore potential confounders (eg, age, sex, co-morbidity) that may be adjusted for in the full-scale RCT. Mean costs (and SDs) will be calculated (with 95% CIs) using published recommendations [46,47]. To account for the amortization of intervention use after upfront costs, we will distribute the investment costs over a 3- to 5-year investment time duration using a 5% societal interest rate and using 3% and 0% rates in the sensitivity analysis. Costs for reported co-interventions (health care services) will be estimated using Alberta costing and using 2015-dollar values.

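### The MCID rule makes the global rating itself the estimate, never ties it to MASC2 change, and conflicts with the plan's own description of the MCID

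*Protocol article*

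**What the plan says.** The Introduction lists as objective 1 to "define a minimal clinically important difference (MCID), as defined by adolescents, for the primary outcome measure". Primary Outcome Measure identifies that measure as the MASC2 total score. Both arms complete it at baseline and at 8 weeks.

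Secondary Outcome Measures then describes the MCID in two ways:
- as a threshold: "Adolescents allocated to the treatment condition are asked to indicate the minimum change in anxiety for which they would consider treatment participation";
- as a rating of change: "To estimate the MCID, we will use adolescents’ global ratings of change on a 10-point Likert scale (-5 to +5), a commonly used anchor".

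The same section sets the timing: "The MCID will be determined for the primary outcome measure following module 8 completion (post-intervention"). Table 1 places the MCID at 8 weeks.

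Statistical Analyses gives the estimation rule. Adolescents' global ratings "within the ranges of +2 to +3 or -2 to -3 for reported change using the 10-point Likert scale) will serve as the estimate" of the MCID. That section mentions MASC2 change scores only for the mean difference between arms and for the SDs that guide the full-scale sample size. It does not mention them in the MCID rule.

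Sample Size expects 40 enrolled and 20 retained per arm by module 8. Secondary Outcome Measures says the MCID will guide interpretation of outcome change in the full-scale trial, and the Discussion says it will inform that trial's methodology.

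**The concern.** In an anchor-based method the global rating selects a group of participants, and the MCID is the change on the outcome scale in that group. Here the rule names the selecting variable as the result. An analyst who follows it reports a value of about 2 to 3 on the rating scale, which cannot be applied to a MASC2 difference.

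Three further points leave the result open:
- **Direction.** One estimate is drawn from a positive and a negative band, and the text does not say that they are analysed apart.
- **Construct.** The smallest change that would make treatment worth taking up is not the same quantity as the change a participant feels has occurred. Only the second is carried into the analysis rule.
- **Scale.** The stated number of points and the stated range disagree, so it is unclear whether a respondent can report no change.

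Two competent analysts could therefore report different MCIDs from the same data. This is the pilot's first objective, and the Discussion relies on the MCID to help clarify inconclusive self-rated treatment effects in earlier trials.

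**Working it through.** **1. Expected respondents (Sample Size).** 160 invited × (1 − 0.50) = 80 enrolled, 40 per arm. 80 × (1 − 0.50) = 40 retained, 20 per arm. The plan's figures reproduce exactly. The MCID item goes to the Breathe arm only, so about 20 of the 40 randomised to Breathe, and none of the 40 controls, are expected to answer it. The article states no MCID value or precision target, so there is no such figure to reproduce.

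**2. Units.** The objective requires MASC2 points. The rule delivers rating points between 2 and 3 in absolute value. No step converts one to the other.

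**3. Scale.** The integers from −5 to +5 number 5 + 1 + 5 = 11. A 10-point scale over that range has to omit zero. The label appears as 10-point in both Secondary Outcome Measures and Statistical Analyses.

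**4. Precision under the anchor reading.** The 95% half-width of a mean, in units of the SD of change within the band, is t(0.975, n − 1)/√n. The share of the 20 respondents in the improved band is an assumption:

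| Share | n | Half-width (SD) |
|---|---|---|
| 20% | 4 | 1.59 |
| 30% | 6 | 1.05 |
| 40% | 8 | 0.84 |
| 50% | 10 | 0.72 |

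As a reference, ratings spread evenly over 11 points would put 20 × 2/11 = 3.6 adolescents in +2 to +3. If both arms were asked (40 retained) and the share were the same in controls, 20%, 30% and 40% would give n = 8, 12 and 16, with half-widths of 0.84, 0.64 and 0.53 SD.

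**5. What signed pooling would do, if it were done.** Suppose improvers and worseners change by the same amount d in opposite directions. With 6 improved and 2 worse, the pooled mean is (6 − 2)/8 × d = 0.5d. With 4 and 4 it is 0. If the MCID were also used as the target difference, required sample size varies as 1/MCID², so halving it multiplies the size by 1/0.5² = 4.

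The same effect in SD units, with d = 0.5 SD and a share w of the combined group rating worse: pooled value = 0.5 × (1 − 2w). Size per arm at 90% power and two-sided 5% (alpha and sidedness assumed) is 2 × (1.960 + 1.282)²/δ².

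| w | Pooled δ (SD) | n per arm |
|---|---|---|
| 0% | 0.5 | 85 |
| 10% | 0.4 | 132 |
| 20% | 0.3 | 234 |
| 30% | 0.2 | 526 |

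These are illustrations of sensitivity, not figures from the protocol.

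**The case against.** The best defence is that the Statistical Analyses sentence is compressed. Secondary Outcome Measures calls the ratings an anchor, the MCID is tied to the primary outcome measure, and MASC2 is collected at the right two times. Mean MASC2 change in the band is therefore the likely intent. This stands as a reading of intent, and it makes the fault repairable. It does not rescue the rule, which names the ratings as the estimate.

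A reader might infer that improvers and worseners will be pooled. The text does not say so; separate MCIDs for improvement and worsening fit the words equally well. What stands is that the rule permits pooling.

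A reader might also infer that the full-scale trial will be sized on this MCID. The article does not state that. It gives the SDs of change as the guide for sample size, and the MCID's stated uses are interpretation and methodology. Use as the target difference is plausible, but the sample-size multiples depend on it.

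Other points carry weight:
- A pilot need not estimate an MCID precisely, so imprecision alone is not an error.
- The within-band SD may be smaller than the overall SD of change.
- Controls may fall in the improved band less often than treated adolescents.
- The 10-point label may be a miscount. A band mean can be computed without a no-change group.
- Table 1 and Primary Outcome Measure allow the 8-week point as well as the end of module 8, so some who do not finish may be asked.

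An article may leave detail to an unseen plan. That does not cover a stated rule that gives the wrong quantity, or two definitions that disagree within one section.

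**Conclusion.** The point holds as a fault in a stated rule. As written, the analysis for objective 1 gives no MCID in MASC2 units, leaves the handling of the two directions open, rests on two unreconciled constructs, and uses a scale whose label and range disagree.

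A reader might conclude that no usable MCID can come from this pilot. That is too strong: with the ratings treated as an anchor and MASC2 available at baseline and week 8, an estimate exists. It would be imprecise, with a half-width of about 1.6 to 0.7 SD of change if 4 to 10 of about 20 respondents fall in the improved band. It would also come mainly from Breathe participants who finish module 8. The band shares are assumed; the 20 is the plan's own figure. The halved MCID and fourfold sample size apply only if signed changes are pooled and the MCID is used as the target difference, neither of which the article states.

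**What to change.** Replace the rule in Statistical Analyses and align Secondary Outcome Measures with it:
- Define the MCID as the mean MASC2 total change from baseline to week 8, with 95% CI, among adolescents rating +2 to +3 (improved).
- Report the −2 to −3 group separately, and never average signed changes across the two groups.
- State whether the scale has a zero. If it does, report mean MASC2 change in the no-change group alongside.
- Name the global rating as the basis of the MCID. Report the item on the minimum change needed to consider treatment under a different name.
- State the number of respondents in each band and that they come from the Breathe arm, mainly after module 8.

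These changes need no new data and cost only wording.

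Optionally, ask the global rating of all participants in both arms at week 8, when controls already complete the MASC2 online. This is one extra item. Because enrolment is under way, controls already assessed would lack it, and any change to the scale would mix versions, so results would have to be reported by version.

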## Results

Currently, adolescents are being enrolled in the study. Enrolment is taking place between March 2014 and February 2016; data collection will conclude May 2016. We expect that analysis and results will be available by August 2016.

## Discussion

As current systems-based models of health care look to enhance local community resource capacity, stepped care options and improved access to mental health services for adolescents are needed. Recent systematic reviews have shown that self-led, computer-based and computer-assisted CBT are viable treatment approaches for adolescents, but suggest that maturation of the evidence base is needed [30,31,32]. This pilot RCT is an essential step to designing a robust RCT to evaluate the effectiveness of Internet-based CBT for adolescents with moderate to mild anxiety problems. As a first step, satisfaction and treatment adherence results will indicate whether we need to make any critical intervention changes prior to a full-scale RCT.

We will use our pilot RCT results to develop a protocol for a full-scale trial. This trial will be designed to test the effectiveness of the *Breathe* program compared to a web-based, minimal control intervention providing psychoeducation (static webpage) in reducing anxiety symptoms in adolescents with moderate to mild anxiety problems. The MCID, sample calculation, and co-intervention use determined from the pilot RCT will inform full-scale trial methodology. Our sample calculation will ensure the full-scale trial is adequately powered, and will address sample size limitations noted in the literature to date [30]. The use of the MCID in the full-scale trial may also help to clarify inconclusive self-rated treatment effects reported across similar trials [30]. Our cost-consequence analysis will inform a cost-effectiveness analysis in the full-scale RCT. Finally, we will use the recruitment and retention rates calculated in the pilot trial to determine the number of study sites and timeline necessary to recruit the full-scale RCT sample.

## Abbreviations

ASQ: Ask Suicide-Screening Questions
Breathe: Being Real, Easing Anxiety: Tools Helping Electronically
CBT: cognitive behavioral therapy
IRIS: Intelligent Research Intervention Software
MASC: Multidimensional Anxiety Scale for Children
MCID: minimal clinically important difference
RCT: randomized controlled trial
SCARED: Screen for Child Anxiety Related Emotional Disorders
SD: standard deviation
